### Recruitment

At Dongyang People’s Hospital, more than 1000 patients seek treatment for vitreous floaters annually, ensuring an ample pool of participants for our studies. Participants will be recruited by ophthalmologists during outpatient visits, without any additional advertising. Interested patients will be invited to discuss the study details with an ophthalmologist. Those who meet all the inclusion criteria will receive complete information regarding their responsibilities and all procedures involved in the trial. Before enrollment, they will be asked to sign a written informed consent form. Insurance coverage, provided for all trial participants, is contracted to compensate for any harm that may occur during the final study visit.

### Intervention

#### YAG vitreolysis procedure

A Karickoff lens with goniosol will be used by the treating physician to perform YAG vitreolysis, with the number of shots determined based on clinical discretion. A focus offset may also be used if necessary, and the treatment will be conducted in single-shot mode with a maximum energy per pulse of 7 mJ. The endpoint of the treatment will be the vaporization of the Weiss ring into gas, as well as the fragmentation of any other vitreous opacities that are considered visually significant by the physician.

#### Sham laser procedure

The same procedure will be followed, but with the laser power turned down to 0.3 mJ and a separate lens covered by a filter that absorbs the power to ensure that no laser energy enters the eye.

### Primary outcome

The study will measure the outcomes at 3, 6, 9, and 12 months. These outcomes include the subjective improvement in floater symptoms, which is rated on a scale of 0 to 10. A score of 0 represents no symptoms, while a score of 10 indicates symptoms that significantly impact daily life. The study also measures the mean change in the National Eye Institute Visual Functioning Questionnaire-25 (NEI VFQ-25), which is a self-reported questionnaire that evaluates a patient’s visual function and its effect on their quality of life. The VFQ-25 consists of 25 items, which assess different domains of vision-related quality of life, including general vision, near and distance activities, driving, social functioning, and mental health. The minimum score for the VFQ-25 is 0, indicating the worst possible visual function and quality of life, while the maximum score is 100, representing the best possible visual function and quality of life. Higher scores on the VFQ-25 indicate better outcomes, indicating that the patient has improved visual function and quality of life. To address multiple comparisons in our study, we applied a Bonferroni correction. This correction method adapts the significance level to maintain an overall alpha level of 0.05, effectively controlling for the heightened risk of type I error associated with multiple testing.

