**Methods:**

The present study is a randomized, controlled, double-blind clinical trial. A total of 70 participants with symptomatic floaters for 1 month were prospectively recruited. These participants will be randomly assigned to two groups, with 35 individuals in each group: the early treatment group and the delayed treatment group. Participants assigned to the early treatment group will undergo YAG laser vitreolysis immediately, followed by a sham laser treatment 3 months later. On the other hand, participants assigned to the delayed treatment group will receive a sham laser treatment and then undergo YAG laser vitreolysis 3 months later. The follow-up time points will be 1, 3, 6, and 12 months from randomization. Primary outcomes will be participants’ self-reported improvement in visual disturbance on a scale of 1 to 10 and their scores on the National Eye Institute Visual Functioning Questionnaire 25 (NEI VFQ-25). Secondary outcomes will be an objective evaluation of the effectiveness of the treatment in reducing vitreous floaters through OCT and fundus photography and tracking any adverse events related to the eyes or overall health.

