### Sample size calculation

The sample size is determined a priori based on calculations assuming a modest improvement of 30% in symptoms in the YAG group compared to 10% in the sham group [7, 15]. This results in a sample of 66 patients with a standard deviation of 25%, an alpha level of 0.05, and a statistical power of 0.9. To account for a 5% rate of lost follow-up, it was decided to include 70 subjects in the study.

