### Statistics analysis

A comprehensive analysis is performed to delineate the demographic and clinical characteristics of the patient population. The normality of the variables is assessed using the Shapiro–Wilk test. The evaluated variables are depicted in tabular form, displaying both absolute and relative frequency distributions. Associations are examined utilizing either Pearson’s chi-square test or Fisher’s exact test, as warranted. The statistical significance of mean differences among quantitative variables is assessed through the paired and unpaired *t*-student tests. To assess variations across different time points within a group, the analysis of variance (ANOVA) with repeated measures is employed.

Continuous data are presented as mean ± standard deviation (SD), while categorical data are represented as counts (percentages). All analyses follow a two-tailed approach, with a significance level of 0.05. The statistical software package SPSS 17 (IBM Corporation, Armonk, NY) is employed for conducting data analysis, by established procedures.

In instances of data discontinuity, missing data will be handled by the “intention-to-treat” principle for conducting inferential statistical analysis. Missing data will be addressed through a dual strategy involving the last observation carried forward (LOCF) method and multiple imputation (MI). Additionally, sensitivity analyses will be conducted to evaluate the influence of various imputation methods on the study outcomes.

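### Months 3, 6, 9 and 12 share primary status, but only month 3, if rated before the second procedure, tests the laser-versus-sham contrast that the trial was sized for

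*Protocol article*

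**What the plan says.** All references are to the protocol article.

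- **Primary outcome:** "The study will measure the outcomes at 3, 6, 9, and 12 months". This applies to both the floater symptom rating and the change in NEI VFQ-25. No time is named as the main one. A Bonferroni correction to an overall 0.05 is promised, without the number of comparisons.
- **Abstract, Methods (arms):** the early group "will undergo YAG laser vitreolysis immediately, followed by a sham laser treatment 3 months later", whereas "participants assigned to the delayed treatment group will receive a sham laser treatment and then undergo YAG laser vitreolysis 3 months later".
- **Abstract, Methods (visits):** "The follow-up time points will be 1, 3, 6, and 12 months from randomization". This list has month 1 and lacks month 9, so it differs from the Primary outcome section.
- **Sample size calculation:** the trial is sized "assuming a modest improvement of 30% in symptoms in the YAG group compared to 10% in the sham group", giving "a sample of 66 patients with a standard deviation of 25%, an alpha level of 0.05, and a statistical power of 0.9". No time point is attached to these figures.
- **Statistics analysis:** "All analyses follow a two-tailed approach, with a significance level of 0.05".
- **Discussion:** the objective has two parts, the efficacy and safety of the laser, and a comparison of early with delayed laser.
- **Methods/design:** the trial is called non-inferiority. No margin, contrast or time goes with that label.

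**The concern.** The design crosses the arms over at month 3. Before that, the randomized comparison is real laser against sham. After it, every participant treated as planned has had one real and one sham session, and the comparison is of timing. The Primary outcome section puts both comparisons under one heading with equal standing.

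The two questions call for different readings of the same result. A laser-versus-sham comparison looks for a clear difference. An early-versus-delayed comparison may well expect a small one, and if the non-inferiority label belongs there, a small difference would be the result sought. With no hypothesis tied to a time, a null finding at month 12 could be reported as lack of laser effect or as no harm from waiting, and the decisive time could be chosen after the data are seen. If the Bonferroni family includes the later times, tests of the timing question also take alpha from the one comparison that was sized.

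**Working it through.** **1. What each listed time compares**

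| Month | Early arm | Delayed arm | Contrast | Months since real laser |
|---|---|---|---|---|
| 3 (if before second procedure) | laser | sham | laser v sham | 3 v none |
| 6 | laser, then sham | sham, then laser | early v delayed | 6 v 3 |
| 9 | same | same | early v delayed | 9 v 6 |
| 12 | same | same | early v delayed | 12 v 9 |

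Three of the four times follow the delayed arm's laser. With two outcomes there are 2 × 4 = 8 outcome-by-time comparisons, of which 2 × 3 = 6 concern timing. On the Abstract's schedule (1, 3, 6, 12), months 1 and 3 are sham-controlled and two of the four times come after the delayed laser.

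The second session also falls at month 3, and the text does not say that the month-3 rating precedes it.

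**2. Reproducing the stated sample size**

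Inputs from the Sample size calculation: difference 30 − 10 = 20 points, SD 25, alpha 0.05, power 0.90. Two-sided testing is from Statistics analysis and 1:1 allocation from Randomization and masking.

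n per arm = 2 × (25/20)² × (1.960 + 1.282)² = 32.84, rounded up to 33, so 66 in total. With 5% loss, 66/0.95 = 69.5, so 70. Both stated figures reproduce. Only a two-sided superiority comparison of two means, laser against sham, is behind them. A noncentral t calculation gives 34 per arm, a trivial difference.

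**3. Power at month 3, 33 per arm, 20-point difference, SD 25**

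| Tests in the Bonferroni family | Alpha per test | Power, normal formula | Power, noncentral t |
|---|---|---|---|
| 1 | 0.05 | 90.1% | 89.3% |
| 2 (two outcomes at month 3) | 0.05/2 = 0.025 | 84.3% | 82.7% |
| 8 (two outcomes, four times) | 0.05/8 = 0.00625 | 69.7% | 66.3% |

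Two assumptions apply. The family size is not stated; eight is the count if each outcome is tested between arms at each listed time. The symptom difference and SD are also carried over to the NEI VFQ-25, for which the documents give neither.

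**4. Power after month 3**

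The documents give no expected early-versus-delayed difference, so a range is assumed (noncentral t, 33 per arm, SD 25, superiority test):

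| Assumed difference (points) | Alpha 0.05 | Alpha 0.00625 |
|---|---|---|
| 15 | 67.0% | 35.6% |
| 10 | 36.0% | 12.4% |
| 5 | 12.6% | 2.6% |
| 0 | 5.0% (type I error) | 0.6% (type I error) |

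Anywhere in this range, power is well below the stated 0.9.

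**The case against.** The strongest reply is that early versus delayed laser is not contamination of the trial but one of its aims. The Discussion states it and presents it as the novel part, and the arms are named for it. That stands. A reader might infer that the later visits are a failed laser-versus-sham comparison, but nowhere does the protocol claim that they compare laser with sham. What is wrong is that two hypotheses share one undifferentiated primary outcome and only one of them is sized.

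Three further inferences are tempting and unsupported.

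- **That the later difference must be about zero because both arms reach 30%.** The 30% and 10% carry no time point, and no value is given for patients after delayed treatment. Zero is one end of an assumed range.
- **That the plan definitely loses power to an eight-test correction.** The count is not stated. It could be two outcomes only, or could include within-group comparisons over time.
- **That month 3 is the only sham-controlled assessment.** Month 1 in the Abstract's schedule is sham-controlled too. The statement is true only of the four times in the Primary outcome section.

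It can also be said that the non-inferiority label fits a later timing comparison, where a small difference would be welcome and superiority power beside the point. This does not rescue the plan: no margin is given, the label is tied to no contrast or time, and the sizing is for superiority.

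Finally, making month 3 the sole primary time is not the only cure. Assigning each hypothesis its own times, or a fixed testing order, would also separate the two questions. Month 3 is preferred here because the sample size supports that contrast and no other.

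**Conclusion.** The point holds as a fault in how the primary comparison is specified. Of the four times given equal primary status, one matches the sized contrast, provided that it is rated before the second procedure. The other three test early against delayed laser at unequal times since treatment, with no hypothesis, margin or sample size of their own. As written, a positive or negative primary result has no single meaning.

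The count of three in four, and of six in eight comparisons, follows from the text of the Primary outcome section. The sample size arithmetic is correct for its own inputs and is not challenged. The power figures are conditional. About 66% against 83% at month 3 assumes an eight-test against a two-test family, with the planned effect and SD for both outcomes. About 5% to 67% after month 3, at alpha 0.05, assumes a true difference of 0 to 15 points. The main conclusion depends on neither set.

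**What to change.** 1. Name month 3, rated before the second procedure, as the primary time for the laser-versus-sham superiority comparison.
2. Label months 6 and later as a separate early-versus-delayed objective, outside the primary Bonferroni family. Report it as a difference with a 95% confidence interval, and state the unequal time since laser (6 v 3, 9 v 6, 12 v 9 months).
3. State how many comparisons the Bonferroni correction covers.
4. Reconcile the non-inferiority label in Methods/design with the superiority sizing. If non-inferiority is meant for the timing question, tie it to a contrast, a time and a margin.
5. Reconcile the Abstract's visit schedule (1, 3, 6, 12) with that of the Primary outcome section (3, 6, 9, 12).

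**Cost.** A protocol and registry amendment with ethics approval, which the protocol requires for any modification. Of the 70 planned participants, 32 were enrolled on the date in Trial status, with recruitment extended to December 2024. The change of primary time itself needs no new visits or patients, but the later times lose primary status.

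There is also a power cost to state openly. If both outcomes stay primary at month 3, power with 33 per arm is about 83%. Restoring 90% would take 2 × (25/20)² × (2.241 + 1.282)² = 38.8, so 39 per arm or 78 evaluable, and 78/0.95 = 82.1, so 83 recruited (normal formula). The stated 90% with 66 evaluable and 70 recruited holds only with a single primary outcome at alpha 0.05.

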### Secondary outcome

The secondary outcomes of the study encompass the objective assessment of changes through OCT and fundus photography. The objective evaluation of vitreous floater improvement using OCT and fundus photography is categorized into five levels: worsening, no change, mild improvement, significant improvement, and complete improvement. The objective evaluation will be conducted at 3, 6, 9, and 12 months.

Other secondary outcomes include the incidence and severity of ocular and systemic adverse events, such as retinal tears, retinal hemorrhage, retinal detachment, lens damage, and other related adverse events. The incidence rates of these adverse events will be recorded immediately after each laser treatment and at 1-month post-treatment.

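### The OCT/fundus grade has five ordered levels, but the only categorical tests the plan names ignore order; an ordinal analysis would add direction, an effect estimate and, for moderate shifts, power

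*Protocol article*

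**What the plan says.** Under Secondary outcome, the protocol article grades change on OCT and fundus photography in a result "categorized into five levels: worsening, no change, mild improvement, significant improvement, and complete improvement". The visits follow: "The objective evaluation will be conducted at 3, 6, 9, and 12 months".

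Under Statistics analysis, the sentence that covers categorical variables is "Associations are examined utilizing either Pearson’s chi-square test or Fisher’s exact test, as warranted". Categorical data are to be shown as counts with percentages. The other methods named are for other kinds of data: "The statistical significance of mean differences among quantitative variables is assessed through the paired and unpaired" t-tests, and repeated-measures ANOVA for change over time within a group. Testing is set by "All analyses follow a two-tailed approach, with a significance level of 0.05". The section names no rank test, trend test, ordinal regression or responder cut, and it does not link any test to the OCT/fundus grade by name.

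The sample size rests on the symptom score, not on this grade: "assuming a modest improvement of 30% in symptoms in the YAG group compared to 10% in the sham group", with "This results in a sample of 66 patients with a standard deviation of 25%, an alpha level of 0.05, and a statistical power of 0.9".

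**The concern.** The grade runs from worse to fully improved, so the question is whether one arm sits higher on that scale than the other. On a table of two arms by five levels, Pearson's chi-square has (2 − 1) × (5 − 1) = 4 degrees of freedom and asks only whether the two patterns differ in any way. Fisher's exact test on the same table is equally blind to order. Neither produces a treatment effect with a confidence interval.

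Two things are at stake. First, a significant p-value would not by itself mean improvement; that would have to be read off the table. Second, spreading the test over four degrees of freedom costs power when the true difference is a shift in one direction. The Background reports a wide gap between objective and subjective response in an earlier sham-controlled trial (94% against 53%), so a reader of this trial will look to the objective grade with some interest.

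**Working it through.** **1. The plan's own sample size reproduces.** Inputs from Sample size calculation: difference 30 − 10 = 20 points, SD 25, two-sided alpha 0.05, power 0.90.

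n per arm = 2 (1.960 + 1.2816)² (25/20)² = 2 × 10.507 × 1.5625 = 32.8, so 33 per arm and 66 in total. Allowing for 5% loss, 66/0.95 = 69.5, so 70. I use 33 per arm below.

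**2. The named tests ignore order.** Take two invented arms of 33, with counts from worst to best of (10, 12, 6, 4, 1) and (1, 4, 6, 12, 10). With equal arms, chi-square = Σ(a − b)²/(a + b) = 81/11 + 64/16 + 0/12 + 64/16 + 81/11 = 22.73, and p = 0.00014 on 4 df. Now exchange the columns for worsening and significant improvement. Chi-square and p are unchanged, because the sum does not depend on column order. The Wilcoxon rank-sum p-value moves from 0.0000025 to 0.85.

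**3. Cost of the extra degrees of freedom, by approximation.** At equal noncentrality, where a 1-df ordered test has 90% power a 4-df test has 74%; where the ordered test has 80%, the 4-df test has 60%. For equal power the 4-df test needs about 1.47 times (at 90%) or 1.52 times (at 80%) the sample.

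**4. Simulation at 33 per arm, two-sided 0.05.** The laser-arm distribution is obtained from the assumed control distribution by a common odds ratio (OR) at every cut of the scale. Four control distributions, worst to best, were assumed: 10/60/15/10/5, 20/20/20/20/20, 10/30/30/20/10 and 5/85/6/3/1 percent, with 20,000 runs each. The ranges are across these four.

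| OR | Chi-square, 2×5 | Wilcoxon rank-sum | Gain, points |
|---|---|---|---|
| 2 | 6–19% | 17–34% | 12–16 |
| 3 | 17–46% | 41–70% | 23–25 |
| 4 | 31–67% | 62–87% | 20–30 |
| 5 | 48–81% | 77–95% | 13–29 |
| 8 | 81–97% | 95–99.5% | 3–14 |

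In the 5/85/6/3/1 case part of the gap arises because chi-square is conservative in sparse tables: its rejection rate under no difference was 1.9%, against 4.6% for the rank-sum test.

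**5. A fifth assumed control distribution, 5/55/25/10/5 percent.** Here 40% of controls improve, an odds of 0.667. At OR 3 the odds become 2.0, so 67% improve in the laser arm.

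| OR | Improved, laser arm | Chi-square | Rank-sum |
|---|---|---|---|
| 2.5 | 62.5% | 28% | 51% |
| 3 | 67% | 42% | 67% |
| 3.5 | 70% | 53% | 78% |
| 6 | 80% | 88% | 97% |
| 8 | 84% | 96% | 99.5% |
| 23.5 | 94% | 100% | 100% |

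The last row is tied to the document's one figure on objective response: 0.667 × 23.5 = 15.7, and 15.7/16.7 = 94%. With 60% of controls improved and 94% in the laser arm, power is 99% against 99.9%. With 10% against 94% improved, both tests are at about 100%.

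**6. Sparse cells.** In step 5 at OR 3, worsening has probability 5% in controls and 1.7% after laser. The expected count per arm is 33 × (0.05 + 0.017)/2 = 1.1. For complete improvement it is 33 × (0.05 + 0.136)/2 = 3.1. Two of the five columns, or 40% of cells, therefore fall below 5, which would point to Fisher's exact test. Changing to Fisher does not restore order. Its power was not simulated.

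**The case against.** The best reply is that the article never assigns chi-square or Fisher to this grade. The sentence is general, the article is condensed, and a fuller analysis plan could name an ordinal method or a responder cut. That stands as a limit on how firmly one may say the plan will use an order-blind test. It does not remove the point, because the article does state the tests for categorical variables and none of them uses order.

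A reader might infer that direction is lost altogether, so that worsening could pass for improvement. The documents do not support this: counts and percentages by arm are to be reported and will show which way the grades moved. Only the test statistic lacks direction.

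A reader might also infer that a real benefit is likely to be missed. That depends on its size. The only objective-response figure in the documents is 94%, and against any of the control rates tried (10%, 40% and 60% improved) both tests would almost certainly detect it. The figure has its own limits. It comes from an earlier trial which, according to the Background, required symptoms for more than 6 months, and the article gives neither a sham rate for it nor a split over five levels. After month 3 both arms will have had the laser, so a smaller contrast at the later visits is plausible, but the documents give no figure for that.

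Finally, the outcome is secondary and the trial was not sized on it. That is correct, and it limits the consequence.

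**Conclusion.** The point holds in a limited form. The grade is ordered, the only categorical tests named ignore order, and so the test has no direction and gives no effect estimate. This part follows from the text and needs no assumption about the data.

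The power loss does need assumptions: 33 per arm, a common odds ratio and invented control distributions. On that footing it is roughly 12 to 30 points for moderate shifts (odds ratios of about 2 to 5), usually 3 to 4 points at an odds ratio of 8, and nil for a contrast as large as the cited 94% suggests. An unconditional claim that power falls sharply, or that this endpoint will fail, would go beyond the documents. The primary outcomes and the safety comparisons are not affected. This is an improvement available at almost no cost, not a flaw that threatens the trial's main conclusion.

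**What to change.** Add one sentence to the statistical analysis section saying that the five-level OCT/fundus grade is compared between arms as an ordered outcome. Use either a proportional-odds model, reporting the common odds ratio and its 95% confidence interval, or the Wilcoxon rank-sum test, reporting the probability that an early-arm eye has the better grade and its 95% confidence interval. Keep chi-square and Fisher's exact test for binary or unordered variables such as the occurrence of an adverse event. Show the five-level table by arm descriptively.

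No further patients, images or gradings are needed. The article requires ethics committee approval and a registry entry for protocol changes, so the administrative cost is that step, if the sentence counts as a modification. It should be fixed before any unblinded look at the grades. Recruitment was still open when the article was written, with 32 enrolled by 19 September 2023.

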Although numerous studies have demonstrated the efficacy and safety of YAG laser vitreolysis, there remains controversy among some researchers regarding its widespread clinical use [9]. They argue that, as with any new treatment modality, moderate skepticism is warranted until further research demonstrates a favorable risk/benefit ratio. Additionally, Shah’s research found that objective improvement in patients’ vitreous floaters was 94%, while subjective improvement was only 53%, indicating a clear disconnect between objective and subjective responses that must be taken into account. On the efficacy front, the majority of current research does not rule out the placebo effect, as symptoms of vitreous opacities themselves may improve with gravity and neural adaptation. Complications of YAG laser are also worth paying attention to, such as lens damage, retinal hemorrhage, retinal vein occlusion, and postoperative high intraocular pressure [10–13]. To reduce intraoperative complications, YAG laser vitreolysis is recommended for patients with stable Weiss rings, with floaters located more than 2 mm away from the retina and more than 5 mm away from the lens [14].

To reduce intraoperative complications, current randomized controlled trials require inclusion criteria of patients with vitreous floaters lasting more than 6 months and completed posterior vitreous detachment [7, 15], which is not clinically practical. Many patients require intervention in the early stages of symptoms. There is a lack of research on the safety and efficacy of early YAG laser vitreolysis. Therefore, we undertook this clinical study to uncover that early YAG laser vitreolysis is both a safe and effective treatment option for vitreous floaters.

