### Data collection, management, and monitoring

Before the trials commence, all investigators undergo comprehensive training on the clinical trial protocol, data management, and indicator evaluation methodology. Throughout the study, investigators diligently collect and record data in the participants’ medical records. All adverse events are carefully documented in the electronic case report form (CRF).

Participants who cannot be followed up for the entire study duration are considered dropouts. Participants have the option to withdraw from the study voluntarily in cases of intolerable side effects or poor treatment efficacy. Additionally, participants can withdraw from the study at any time for any reason. The investigators have the authority to withdraw participants from the study to prioritize their safety.

Any modifications to the study protocol require prior approval from the institutional ethics committee at Dongyang People’s Hospital. Once approved, these changes must be documented in the trial registry and subsequently included in the final research data report. Significant protocol amendments will be effectively communicated to trial participants through various channels, including written notifications, verbal explanations, or informational sessions. Participants will be given opportunities to seek clarification, ask questions, or express any concerns they may have.

During the experiment, concurrent treatments such as chronic diabetes, hypertension, anxiolytics, and antidepressant drugs are accepted. After all the follow-ups, participants are asked about receiving any other interventions during the study period, and this information is reported in the study results.

To minimize data loss, all participants are provided with guidance when they sign the informed consent form and commit to attending the scheduled treatment dates. Participants receive an appointment card to attend sessions. An evaluator is responsible for notifying and monitoring the participants every week (via telephone contact, WeChat, and/or email) and accompanying them during the research.

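### The adverse-event outcome names no time point beyond 1 month after each laser, and its check after the second procedure (month 4) is in neither printed schedule

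*Protocol article*

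**What the plan says.** The abstract (Methods) sets the procedures. The early group "will undergo YAG laser vitreolysis immediately, followed by a sham laser treatment 3 months later"; the delayed group "will receive a sham laser treatment and then undergo YAG laser vitreolysis 3 months later". It then gives the schedule: "The follow-up time points will be 1, 3, 6, and 12 months from randomization".

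The Primary outcome section gives a different list: "The study will measure the outcomes at 3, 6, 9, and 12 months". The Secondary outcome section repeats that list for OCT and fundus photography: "The objective evaluation will be conducted at 3, 6, 9, and 12 months".

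For ocular and systemic adverse events, with retinal tear, detachment and lens damage among the examples, the Secondary outcome section has its own rule: "The incidence rates of these adverse events will be recorded immediately after each laser treatment and at 1-month post-treatment".

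The section on data collection, management and monitoring adds: "All adverse events are carefully documented in the electronic case report form (CRF", with no time limit. It also provides weekly remote contact with participants, and a monitoring board that looks at safety data on a 3-monthly cycle.

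Safety is a stated aim. The Background closes with "we undertook this clinical study to uncover that early YAG laser vitreolysis is both a safe and effective treatment option for vitreous floaters", and the Discussion makes the comparison of safety between early and delayed laser part of the objective.

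**The concern.** Two things do not fit together.

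First, the adverse-event rule implies a check 1 month after the second procedure, and no printed list of times contains it. For the delayed arm that procedure is the active laser, so the missing time point is the one that matters most for that arm's laser safety.

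Second, the rule ties incidence to the procedure itself and to 1 month after it. It does not say what happens to a retinal tear, detachment or lens injury first found at, say, month 6 or 12. The case report form should hold such an event, but the outcome definition does not clearly include it.

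At stake is the early-versus-delayed safety comparison. Two analysts following the text could build different event counts from the same database, one stopping at 1 month after each laser and one running to month 12.

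**Working it through.** The plan attaches no figure to this point. The check sets its time points side by side.

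**Inputs.** Procedures at months 0 and 3 (abstract, taking the immediate laser to be at randomization). Adverse-event check at procedure + 1 month (Secondary outcome). List A: 1, 3, 6, 12 (abstract). List B: 3, 6, 9, 12 (Primary and Secondary outcome). End of follow-up: month 12.

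**Step 1: is the 1-month check on a list?**

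| Procedure | Time | + 1 month | List A | List B |
|---|---|---|---|---|
| First (active in early arm, sham in delayed arm) | 0 | 0 + 1 = 1 | yes | no |
| Second (sham in early arm, active in delayed arm) | 3 | 3 + 1 = 4 | no | no |

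In both lists the first time after the second procedure is month 6, which is 6 − 3 = 3 months after it.

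**Step 2: how much follow-up lies beyond the last named adverse-event time?**

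- Early arm: 12 − 0 = 12 months after active laser, of which 12 − 1 = 11 lie beyond the 1-month check.
- Delayed arm: 12 − 3 = 9 months after active laser, of which 9 − 1 = 8 lie beyond it.

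These figures apply only if the outcome is read strictly, as ending at the 1-month check.

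**Step 3: what equal window is available?** The longest window that both arms can complete is the smaller of 12 and 9, that is 9 months: months 0 to 9 in the early arm and months 3 to 12 in the delayed arm.

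**Step 4: which listed times fall in that window, counted from active laser?**

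| List | Early arm | Delayed arm |
|---|---|---|
| A | 1, 3, 6 | 6 − 3 = 3, 12 − 3 = 9 |
| B | 3, 6, 9 | 6 − 3 = 3, 9 − 3 = 6, 12 − 3 = 9 |

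List B lines the arms up and List A does not. Which list governs therefore affects the safety comparison as well as the efficacy outcomes.

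**Step 5: what can each period show?** Over months 0 to 3 one arm has had active laser and the other sham, so the contrast bears on laser harm. After month 3 every participant treated as planned has had one of each. Later comparisons therefore need to be counted from each arm's active laser.

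**The case against.** The strongest reply is that the adverse-event sentence is its own schedule. It applies to each laser treatment, so both arms get an immediate and a 1-month check after both procedures. The two printed lists need not be complete visit schedules: List B times efficacy and imaging outcomes, and List A comes from an abstract. The full schedule is in the SPIRIT figure, which is not available here and may show a month-4 contact. All adverse events are entered in the case report form, weekly contact continues, and a monitoring board reviews safety.

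Much of this stands, and it rules out three stronger readings that a reader might infer.

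- *That later events are discarded.* The rule does not say it is exclusive, and the case report form takes all adverse events. The open question is whether they are counted.
- *That the arms are ascertained unequally by design.* The rule covers each procedure. The mismatch in Step 4 arises only if List A is the complete schedule, and the text does not establish that.
- *That the safety comparison is defective because 35 per arm is small for rare events.* That is true of any trial of this size whatever its schedule, and nowhere does the article say that a non-significant test will be taken as proof of safety.

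The reply does not supply a named time after 1 month in the outcome definition, or agreement between that definition and the printed lists. Nor does remote contact close the gap: it can pick up symptoms, but it is not an eye examination. Condensation for a journal does not explain the mismatch, because the article does print these time points and they do not agree.

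**Conclusion.** The point holds in a limited form. The 1-month check after the second procedure falls at month 4 and matches neither printed list. The stated incidence outcome has no time point beyond 1 month after a laser, although participants are followed to month 12. Later ocular events may therefore be collected yet not enter the incidence used for the early-versus-delayed comparison.

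Its size is a span of follow-up, not a number of events: on the strict reading, 11 of 12 months after active laser in the early arm and 8 of 9 in the delayed arm. The article gives no adverse-event rates, so the number of events affected, and the direction of any effect on the conclusion, cannot be stated.

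This assumes that the first procedure is at randomization, the second is 3 months later, and the SPIRIT figure does not already settle the schedule. If that figure shows a month-4 check, the schedule mismatch becomes a matter of wording, but the missing later time point remains. The point deserves correction because safety is half of the trial's question. It is a matter of definition and does not undermine the design.

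**What to change.** 1. Reconcile the abstract, the Primary outcome section, the Secondary outcome section and the data collection section, so that one schedule shows where the 1-month post-treatment check falls after each procedure and whether months 1 and 9 are visits.

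2. Define the safety outcome as all ocular adverse events in the case report form from the first procedure to month 12, keeping the immediate and 1-month counts as named sub-periods.

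3. Report two comparisons, each with exact 95% confidence intervals:
   - (a) YAG against sham over months 0 to 3, counting only events before the second procedure;
   - (b) early against delayed YAG over an equal window after each arm's active laser, up to 9 months, among those who received it.

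4. State that the windows in (b) start at different times since symptom onset: about 1 month in the early arm and about 1 + 3 = 4 months in the delayed arm. Events unrelated to the laser may therefore differ between them, which is why (a) should stand beside (b).

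The cost is small: revised wording, event dates from the case report form (assumed to be recorded there), slightly more analysis, and a more cautious safety statement. No treatment or dose changes. The article reports 32 of 70 participants enrolled at 19 September 2023 and recruitment extended to December 2024; on that status the definition could be settled before the data are analysed.
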